### Secondary outcomes

The secondary aims are to explore the acceptability and usability of the RC training intervention, and changes in RC, quality of care, job satisfaction, and intent to stay among participants following the RC training intervention.

#### Acceptability

Acceptability of the intervention and study procedures will be assessed qualitatively via focus group interviews. We will use Yardley et al. [29] person-centered approach to gain an in-depth understanding of the beliefs, needs, and attitudes of the participants who participate in the RC training intervention. We selected the person-based approach to better understand how different healthcare professionals (e.g., nurses versus physicians) on different units (e.g., medical-surgical versus ICU) experience and engage with the RC training intervention. Additionally, we desire to explore which components of the RC training intervention are relevant and useful and which components of the training intervention are not [29]. Verbal consent will be obtained from participants to audio record the RC training intervention sessiocns. We will create an Excel spreadsheet to capture participant responses from the training sessions and explore similarities and differences in participant responses. The Excel files from the RC training interventions will be stored on a password-protected computer. We will explore nurses’ and physicians’ views and experiences of the RC training intervention, including what they perceive to be barriers to conducting the intervention. Focus group interviews will help the research team to (1) refine the intervention; (2) determine if the measures we selected align with the experiences of the participants; and (3) better understand the outcomes in Aim 2 (e.g., group-level changes in RC and individual-level changes in quality of care, job satisfaction, and intent to stay).

### Outcomes

This study is not powered to detect statistically significant changes in group and individual-level outcome measures. However, we will collect data on these outcomes to explore the feasibility of collecting these outcomes in a larger, powered study and conduct some exploratory analyses.

#### Group-level outcomes: RC

The RC survey is a seven-item instrument based on the RC framework [10, 11]. RC is measured between professional roles rather than between unique individuals [10]. Each RC dimension is summarized using a mean score, whereas the total RC index is a newly generated variable of a mean score for all seven dimensions [10, 11]. We will calculate RC scores for all participants (e.g., LPNs, RNs, physician residents, and physicians). A sample question is: How frequently do healthcare professionals in each of these groups communicate with you about patient care? See Additional file 1 for items and scoring. See Table 5 for the psychometric properties of study variables.

**Table 5 Tab5:** Psychometric properties of study variables

Instrument	Number of items	Response format	α	Validity and factor analysis
Relational coordination	7	Varying response scale (Scores range from 7 to 35 and higher scores indicate greater RC)	0.8	Convergent exploratory factor analysis
Quality of care	3	Varying response scale (lower scores indicate higher quality of care)	–	–
Job satisfaction	3	1 single-item measure 2 open-ended questions	–	–
Intent to stay	4	1 = “strongly disagree,” 2 = “disagree,” 3 = “neither agree nor disagree,” 4 = “agree,” 5 = “strongly agree.”	0.85 (civilian participants) 0.91 (military participants)	Convergent and discriminant Exploratory factor analysis

#### Individual-level outcome: quality of care

Quality of care, defined as the extent to which healthcare services provided to individuals and patient populations improve desired health outcomes [30], will be explored from the healthcare professionals’ perception. Healthcare professionals view quality of care in terms of attributes of care, results of care, and the characteristics of patient and provider interactions [31]. We will explore the quality of care using three questions. These three questions demonstrated validity and reliability for use in a previous federally funded research study [32]. See Additional file 1.

#### Individual-level outcome: job satisfaction

Job satisfaction, defined as the extent to which people like their job [33], will be explored using three questions (one single-item measure and two open-ended questions). Single-item measures of job satisfaction show a strong correlation with multiple-item scales [34]. Thus, we selected a single-item measure to reduce participant response burden. We asked participants, “On the whole, how satisfied are you with your present job?” Responses range from “1 = very dissatisfied” to “5 = very satisfied,” with higher scores indicating better job satisfaction. See Additional file 1.

#### Individual-level outcome: intent to stay

Intent to stay, defined as the extent to which employees plan to continue working with their employer, will be measured using a 4-item intent to stay scale [33]. Responses range from “1 = strongly agree” to “5 = strongly disagree.” We will use reverse scoring where appropriate so that higher scale scores will indicate higher intent to stay. See Additional file 1 for items and scoring.

### Demographic variables

We will also collect data regarding participants’ demographic characteristics (race, sex, age, experience, education level, length of time worked on the unit, and certifications).

### Evaluations

We will use an RC knowledge assessment to explore participants’ understanding of RC at baseline and 2 weeks after each RC training intervention session. See Additional file 2 for items and scoring. Additionally, we will administer an RC training evaluation to explore participants’ experiences with the face-to-face RC training intervention. See Additional file 3.

### Data analysis

#### Quantitative analysis

Data spreadsheets will be imported into Stata (StataCorp, College Station, TX) [35]. Standard descriptive statistics (e.g., means and standard deviations for continuous variables such as age and percentage for categorical variables such as sex) will be used to summarize demographic variables. Acceptability will be assessed qualitatively (see the “ Qualitative analysis” section below).

Aim 1: Determine the feasibility of conducting an RC training intervention.

All feasibility outcomes will be summarized with descriptive statistics overall and by group. As this is a pilot study, the level of missing data will be documented, but imputation will not be performed.

Aim 2: To explore the acceptability of the RC training intervention.

### Qualitative analysis

*Focus group interviews*. Data analysis will be concurrent with data collection to monitor for data saturation. Participants’ responses will be transcribed verbatim, and two researchers will independently verify the accuracy of the Excel spreadsheet compared to the original Word file notes. Thematic analysis will be used to analyze qualitative interview data since it offers an organized method that allows the researcher to identify, analyze, and report themes [36]. Additionally, thematic analysis is a flexible method that offers the researcher the ability to focus on the meaning expressed by study participants and the identification of themes across interviews to produce an in-depth and rich account of the data [37]. The six steps of thematic analysis as described by Braun and Clark [36] are (1) familiarization of the data, (2) generation of codes, (3) combining codes into themes, (4) reviewing of themes, (5) determining the significance of themes, and (6) reporting of findings. The research team will initially read the transcripts to become familiar with the data. Transcripts will be re-read with the initial generation of codes. The research team will meet on a regular basis to discuss the codes being generated and to reach a consensus on any discrepancies. As the analysis progresses, the team will determine themes. Our approach to rigor will be guided by Morse et al. [38] who recommend verifying the data during the process of data analysis by “checking, confirming, making sure, and being certain” (p. 12). Reflexivity will be maintained through discourse regarding personal beliefs and judgments brought up by research team members in the process of analysis, with assumptions and interpretations verified by returning to the data [39]. See Additional file 4 for focus group interview questions.

Group-level and individual-level changes in RC.

We will also explore group-level changes in RC and the individual-level changes in quality of care, job satisfaction, and intent to stay among nurses and physicians following an RC training intervention). We will plot the individual changes over time using line graphs and estimate changes over time with point estimates and 95% confidence intervals. For RC, we will also create RC matrices and maps at each time point to further describe RC by professional role.

### Data monitoring and management

The research team will be responsible for data monitoring and ensuring that participants meet the inclusion criteria to participate in this study. Data from the online surveys will be stored on RedCAP, an encrypted and secure platform. Participants will scan a QR code to complete the surveys, and all surveys, comments, and annotations will be stored on RedCAP to ensure the data is properly protected from unauthorized users. We will name all files and folders by professional role and unit type. Files will be backed up twice during data collection from RedCAP to Stata to prevent accidental changes or partial/complete deletion of data or damage caused by computer viruses. A password and username will be required to access the data. The research team will be the only people who have access to the data.

### Reporting of adverse events

The research team does not expect that participants will experience adverse events given there is minimal risk related to this training intervention. However, the research team will continuously monitor participants for adverse events and unanticipated problems by physically observing the participants during the study (RC training intervention and focus group interviews). The principal investigator will report adverse events and unanticipated problems to the institutional review board. The research team will review the risk of adverse events and unanticipated problems weekly during data collection and we will adjust the protocol as needed. We will use the Common Terminology Criteria for Adverse Events v3.0 (CTCAE) to grade the severity of an adverse event.

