## Background

Patient care is becoming more complex, as patients are presenting with uncertain diagnoses and multiple co-morbidities [1, 2]. This is a critical problem within the healthcare system as healthcare professionals are challenged to meet the increased time constraints and demands that accompany caring for complex patients. As patient care becomes more complex, high-quality communication and relationships among healthcare professionals are critical to coordinating care [3–6]. While uncoordinated care is a problem in civilian healthcare settings, military healthcare settings may encounter additional barriers to coordinating care because of the unique hierarchical ranking structures that exist among healthcare professionals in military hospitals [7, 8]. Understanding RC in a military context poses a unique opportunity to examine a complex organizational structure due to the presence of clear authority gradients and differences in military rank. Additionally, explicit, formal power differences exist between enlisted service members, commissioned officers, and members in different ranks within each personnel structure. These hierarchical ranking structures create power differences among healthcare professionals in different ranks. Power differences among members in a workgroup can negatively influence communication and relationships [9], leading to lower job satisfaction and retention.

Relational coordination (RC), defined as “a mutually reinforcing process of communicating and relating for the purpose of task integration within and between roles,” ([10] p. 301) is a unique way to coordinate care among healthcare professionals involved in complex work processes. RC encompasses four communication dimensions (frequent, timely, accurate, and problem-solving communication) and three relationship dimensions (shared goals, shared knowledge, and mutual respect) [10, 11] See Table 1.

**Table 1 Tab1:** Dimensions and definitions of relational coordination [10, 11]

Seven relational coordination dimensions	Definitions
Frequent communication	How often professionals communicate regarding their work process
Timely communication	How soon professionals report significant information regarding a work process
Accurate communication	Preciseness of information communicated between professionals regarding a work process
Problem-solving communication	The extent to which professionals seek solutions instead of placing blame when problems occur

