### The RC training intervention

The RC training intervention will be conducted face-to-face after participants complete the baseline survey and RC knowledge assessment. See Additional files 1 and 2. The RC training intervention will be delivered by a member of the relational coordination collaborative group. The relational coordination collaborative group is a community of professionals from various sectors around the world who use RC in their research and practice. A 1-h RC training session will be delivered each month for 3 months, for a total of three sessions. Session one will explore the RC dimensions and evidence-based literature supporting RC and patient and staff outcomes [20, 23, 24]. Session two will be conducted 1 month later and focus on a relational mapping exercise. Relational mapping allows participants to generate new ideas for how they communicate and relate to each other regarding complex work processes [25]. Session three will be conducted 1 month after session two and will explore how to operationalize RC on their unit [26]. During the third RC training session, we will help participants identify effective strategies to improve interprofessional collaboration, quality of care, job satisfaction, and intent to stay using the dimensions of RC. See Table 2. Participants will be advised that may leave the RC intervention training sessions for any reason and at any time if they.

**Table 2 Tab2:** RC training intervention overview

Relational coordination training session 1 (1 h lunch and learn)	
Objectives	• Discuss the relational coordination dimensions and organizational change model • Review relational coordination and patient and staff outcome studies
Relational coordination training session 2 (1 h lunch and learn)	
Objectives	• Participants will create color-coded relational ties between healthcare professionals involved with patient care on their unit • Identify which healthcare professionals have weak relational ties • Identify which healthcare professionals have strong relational ties • Discuss why these weak and strong relational ties exist and ways to improve weak relational ties among healthcare professionals
Relational coordination training session 3 (1 h lunch and learn)	
Objective	• Discuss how to operationalize the relational coordination dimensions • Discuss how relational coordination can be used in conjunction with TeamSTEPPS to improve patient and staff outcomes

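### The only stated way of finding adverse events is watching participants in sessions and focus groups, so problems on the unit or among people who stop attending are likely to be under-ascertained

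*Protocol article*

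**What the plan says.** The section Reporting of adverse events starts from the position that the team "does not expect that participants will experience adverse events given there is minimal risk related to this training intervention". It then gives one method of finding events, which is to "continuously monitor participants for adverse events and unanticipated problems by physically observing the participants during the study (RC training intervention and focus group interviews"). Around that method it sets a weekly review ("The research team will review the risk of adverse events and unanticipated problems weekly during data collection"), reporting by the principal investigator to the institutional review board, and severity grading by CTCAE v3.0.

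Other sections fix the observed contacts. The RC training intervention section gives three 1-h sessions a month apart. Study procedures adds an invitation to a focus group of 30 to 45 minutes, two weeks after the last session. Participants "may leave the RC intervention training sessions for any reason and at any time" (the sentence is incomplete in the text available). Sampling and recruitment plans for 36 to enrol and 18 to complete.

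Electronic surveys are also sent two weeks after each session. They cover RC, RC knowledge, quality of care, job satisfaction (including two open-ended questions) and intent to stay. Comments are stored, and an evaluation follows each session. None of these is mentioned in connection with adverse events.

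**The concern.** The stated method fits poorly with where a harm from this training would most plausibly appear. The Background says of military hospitals that "Power differences among members in a workgroup can negatively influence communication and relationships", with consequences for job satisfaction and retention. One objective of session 2 in Table 2 is to "Identify which healthcare professionals have weak relational ties", followed by discussion of why those ties are weak. If that exercise caused friction, much of it would arise later on the unit, where no observer is described. A person who stops coming is also no longer observed, and the article describes no record of why someone left. A departure because of discomfort could then appear only as non-retention against Table 4.

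What is at stake is how a safety statement would be read. The article commits to grading and reporting events, and the study is meant to refine procedures before a larger randomized trial. A result of no events, obtained mainly by watching people in a room, could be taken as firmer support for minimal risk than the method allows.

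**Working it through.** **The plan's own figures.** The article states no figure for adverse events. Its one precision figure is the 17% margin for the completion rate. With x = 18 and n = 36, the two-sided 95% Clopper-Pearson interval is 32.9% to 67.1%, a half-width of 17.1%. The figure reproduces, but it does not bear on how harms are found.

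**Observed time.** The inputs are three 1-h sessions, a focus group of 0.5 to 0.75 h, two one-month gaps between sessions, and two weeks from session 3 to the focus group.

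- Maximum observed time per participant: 3 × 1 h + 0.5 to 0.75 h = 3.5 to 3.75 h.
- Span from session 1 to the focus group: about 61 + 14 = 75 days, and 75 / 7 = 10.7 weeks, so roughly 10 to 11 weeks.
- Share of working time, assuming a 40-h week (the article gives no working hours): lowest 3.5 / (11 × 40) = 0.80%, highest 3.75 / (10 × 40) = 0.94%.
- Someone who attends session 1 only: 1 / (10.7 × 40) = 0.23%.

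These shares show that the stated method is not continuous. They are not detection probabilities, because one focus group can bring out events from the whole period.

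**People who stop.** The plan expects 36 − 18 = 18 enrollees not to complete, so up to half may be unobserved at the later contacts.

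**What a zero count would show.** Suppose every event in the people observed were seen and none occurred. The one-sided 95% upper bound on the event proportion is 1 − 0.05^(1/n):

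- n = 36: 8.0%
- n = 18: 15.3%

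These are best-case bounds. Incomplete ascertainment makes a zero count less informative than they suggest.

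**Other contacts set beside the adverse-event section.**

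| Contact | Could it bring out a unit-level problem? | Linked to adverse-event review? |
|---|---|---|
| Sessions 2 and 3 (audio recorded) | Yes, if raised | Observation only |
| Focus group | Yes; it covers experiences and barriers | Observation only |
| Two-week surveys, with two open-ended job satisfaction questions | Incidentally | No link stated |
| Stored survey comments | Incidentally | No link stated |
| Session evaluations | Incidentally | No link stated |

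**The case against.** The strongest reply is that problems on the unit have several ways to reach the team. The focus groups are themselves a named monitoring contact and invite participants to describe their experience. Sessions 2 and 3 take place after people have been back at work, and the recordings are reviewed. The surveys measure RC, job satisfaction and intent to stay two weeks after every session and include free text. No stated rule ends the surveys for someone who leaves a session. This stands, and it limits the point. A reader might infer that harms on the unit cannot be detected, or that the study is bound to report none. The documents do not support either inference, since an event visible in the room, or raised there, can be recorded and reported.

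Other parts also stand. The Background presents power differences as a feature of the setting, not as a risk of the training, so the route to harm is plausible but inferred. That the people most affected would be the ones to leave is not shown. Acceptability does not rest only on those who stay for the focus group, because session evaluations contribute as well. Nor should weekly reviews be counted against four observation occasions per unit: three units on staggered dates could give up to 3 × 4 = 12 occasions, and surveys arrive in between.

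It can also be said that a condensed article may leave a self-report route to the full protocol, and that the survey items, evaluation and focus-group questions are in additional files not shown. That is a fair caution about what those files contain. It does not remove the point, because the article does not leave the method open: it names one and calls it continuous.

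**Conclusion.** The point holds in a limited form. Physical observation in sessions and focus groups is the only detection method stated. It covers at most 3.5 to 3.75 h per participant over about 10 to 11 weeks, under 1% of working time if a 40-h week is assumed, and so does not support the description as continuous. Problems between sessions, or among people who stop attending, are likely to be under-ascertained. A report of no adverse events would be weak evidence of no harm: even with perfect observation it would leave an upper bound of 8.0% with 36 people or 15.3% with 18.

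The severity is modest. No feasibility benchmark in Table 4 depends on adverse events, and the primary and secondary conclusions do not rest on them. The judgement assumes that the additional files contain no harm question feeding the adverse-event review; if they do, the remedy reduces to saying so in this section.

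**What to change.** Keep the observation and build on contacts that already exist:

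1. Add one item to each of the three two-week post-session surveys asking whether taking part has led to any unanticipated problem or negative consequence since the last session, with space to describe it.
2. Record the reason when a participant leaves a session early or withdraws, and offer the same item to those who withdrew unless they decline contact.
3. State that these items, the open-ended survey comments and the focus-group remarks feed the weekly review and the reports to the institutional review board.
4. Report adverse events with the number of people asked as the denominator, and describe how events were sought.

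The cost is a slightly longer survey, some unrelated complaints to sort through, and a minor amendment; no extra visits are needed. Table 3 places the sessions and focus groups in the third quarter of 2023. If collection has ended, the fourth step still applies in part: say that events were sought by observation, interpret a zero count accordingly, and carry the other steps into the larger trial.
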